### Outcomes

2.4

#### Primary efficacy outcome

2.4.1

The primary efficacy outcome will be the change in ISI score from baseline to the end of the 4-week treatment period. The ISI is a validated 7-item self-report measure that has demonstrated strong internal consistency and construct validity for evaluating insomnia severity in cancer patients (20). ISI scores are categorized as follows: 0–7 (no clinically significant insomnia), 8–14 (mild insomnia), 15–21 (moderate insomnia), and 22–28 (severe insomnia) (21). ISI assessments will be conducted at baseline, as well as at weeks 2, 4, 6, and 8 following the start of treatment.

#### Secondary efficacy outcomes

2.4.2

Changes in ISI scores from baseline at all additional assessment time points.Treatment response rate, defined as the percentage of participants achieving a reduction of ≥8 points in ISI score from baseline at each assessment (22).Changes in hypnotic medication usage. To maintain consistency in subsequent analyses and reporting, all hypnotic doses will be converted to standardized diazepam equivalent doses. For participants using hypnotic medications, the average dosage over the preceding 2 weeks will be recorded at baseline, as well as at weeks 2, 4, 6, and 8 after treatment initiation.Changes in Pittsburgh Sleep Quality Index (PSQI) scores. The PSQI is a widely used questionnaire to assess sleep quality over the past month, comprising seven components that evaluate specific sleep-related features (23). Scores range from 0 to 21, with 0–5 indicating good sleep quality, 6–10 suggesting moderate sleep quality, 11–15 reflecting poor sleep quality, and 16–21 indicating very poor sleep quality. Assessments will be conducted at baseline, as well as at weeks 4 and 8 post-treatment initiation.Changes in Piper Fatigue Scale (PFS) scores. The PFS is a validated tool widely used to assess fatigue in cancer populations (24), evaluating four dimensions: behavioral, affective, sensory, and cognitive. Scores range from 0 to 10, with 0–3 indicating mild fatigue, 4–6 indicating moderate fatigue, and 7–10 indicating severe fatigue. Assessments will be conducted at baseline and at weeks 4 and 8 post-treatment initiation.Quality of life, assessed using the Functional Assessment of Cancer Therapy-Breast (FACT-B) scale, which includes a general cancer subscale (27 items) and a breast cancer-specific subscale (9 items) (25). Higher scores on the FACT-B indicate better quality of life. Assessments will be conducted at baseline, and at weeks 4 and 8 post-treatment initiation.

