#### Inclusion criteria

2.2.2

Age range of 18 to 75 years.Female patients with a pathological diagnosis of breast cancer, stages I to III, according to the American Joint Committee on Cancer (AJCC) 8th edition staging system.Completion of primary breast cancer treatment (e.g., surgery, radiotherapy, chemotherapy, targeted therapy, or immunotherapy) for a minimum of 3 months, with the exception of ongoing endocrine therapy, which is permissible if administered for over 3 weeks.No signs of cancer recurrence or new primary tumor development.Diagnosis of chronic insomnia as defined by the Diagnostic and Statistical Manual of Mental Disorders, 5th edition (DSM-5) (18), according to criteria set by the American Psychiatric Association.Insomnia severity ranging from mild to severe, represented by an ISI score of 8 or higher.

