### Randomization

2.6

An independent biostatistician will generate the randomization sequence using a stratified block randomization design. Block sizes of 2 or 4 will be used, with stratification based on whether patients are currently receiving endocrine therapy (yes or no). Participants will be assigned to either the LSM or WC groups in a 1:1 ratio. The randomization codes will be sealed in sequentially numbered, opaque envelopes, which will be securely maintained by independent administrative staff. Participants will receive their envelopes in the order of enrollment to determine their group allocation.

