### Statistical analysis

2.9

The analysis will be conducted based on the intent-to-treat (ITT) population, defined as participants who complete baseline assessments and have at least one follow-up measurement. The Shapiro–Wilk test will be employed to assess the normality of the data distribution. For continuously measured repeated data, such as ISI scores, PSQI scores, PFS scores, FACT-B scores, and hypnotic medication dosages, a mixed-effects model adjusted for baseline values will be used to compare longitudinal changes from baseline across follow-up time points between groups. The model will include fixed effects for endocrine therapy status (yes or no), time, group, and the interaction between time and group, while treating individual participants as random effects. Given that mixed-effects models can accommodate participants with at least one outcome measurement, no imputation will be performed for missing values in the primary analysis (30).

For non-repeated continuous variables, such as serum biochemical markers and gut microbiota abundance, between-group comparisons will be performed using either the *t*-test or Mann–Whitney *U* test, depending on data distribution. Categorical variables, including treatment response rates and incidence of adverse events, will be analyzed using chi-square or Fisher’s exact tests. Correlation analyses between ISI scores, differential serum biochemical markers, differential metabolites, and key gut microbiota will be performed using Pearson or Spearman correlation coefficients. Missing values for data analyzed using non-mixed effect models will be managed using multiple imputation methods.

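### The 8-point ISI response rate is tested without adjustment for baseline or stratum, and its threshold is stricter than leaving the insomnia range for every mild entrant

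*Protocol article*

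**What the plan says.** All references are to the protocol article.

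- **Entry (2.2.2, Inclusion criteria):** "Insomnia severity ranging from mild to severe, represented by an ISI score of 8 or higher".
- **ISI bands (2.4.1, Primary efficacy outcome):** "0–7 (no clinically significant insomnia), 8–14 (mild insomnia), 15–21 (moderate insomnia), and 22–28 (severe insomnia".
- **Response (2.4.2, Secondary efficacy outcomes):** "defined as the percentage of participants achieving a reduction of ≥8 points in ISI score from baseline at each assessment". No outcome based on reaching the lowest band is listed.
- **Randomisation (2.6):** blocks are used "with stratification based on whether patients are currently receiving endocrine therapy (yes or no".
- **Test (2.9, Statistical analysis):** "Categorical variables, including treatment response rates and incidence of adverse events, will be analyzed using chi-square or Fisher’s exact tests". No covariate or stratum is named. In the same section the repeated continuous outcomes go to a mixed model with the baseline value and endocrine status as covariates.
- **Missing data (2.9):** "Missing values for data analyzed using non-mixed effect models will be managed using multiple imputation methods".

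**The concern.** There are three linked weaknesses, all in a secondary outcome.

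1. Section 2.9 adjusts the ISI score for baseline and for the randomisation stratum, then drops both when the same score is cut into response. If either variable predicts response, precision is lost for no saving, because both are already collected.
2. The trial admits people from ISI 8 upwards but requires the same 8-point fall of all of them. A mild entrant can leave the insomnia range and still be a non-responder, while a fall from 28 to 20, which is still moderate, is a response.
3. The imputation sentence covers everything outside the mixed model. That includes a test with no standard way to pool (Fisher's) and, read literally, adverse events.

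At stake are the precision and readability of the response rate, not the trial's main conclusion.

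**Working it through.** **The plan's own figure.** The article gives none for response. Its sample size rests on mean change and reproduces from the pilot values in section 2.8. Pooled SD = √((4.06² + 2.38²)/2) = 3.328, and d = (6.82 − 3.24)/3.328 = 1.08. Unequal-variance t-test power is 0.893 at 19 and 0.909 at 20 per group; 20/0.90 = 22.2, so 23; 23 × 2 strata = 46. The steps 20 and 23 are not printed in the article; they are the route that reaches its 46. Nothing below alters this.

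**Step 1: the threshold.** For baseline b, response needs a score of b − 8 or less. Reaching ISI 7 needs a drop of only b − 7.

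| Baseline b | Highest score that is a response | Drop needed to reach 7 | Scores in 0–7 counted as response | Scores in 0–7 missed |
|---|---|---|---|---|
| 8 | 0 | 1 | 1 of 8 | 1–7 |
| 11 | 3 | 4 | 4 of 8 | 4–7 |
| 14 | 6 | 7 | 7 of 8 | 7 |
| 15 | 7 | 8 | 8 of 8 | none |

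Over baselines 8 to 14 the rule counts 1 + 2 + … + 7 = 28 of 7 × 8 = 56 baseline-and-score pairs. This counts pairs, not patients.

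**Step 2: the test.** The article gives no response rates by stratum, so all rates here are assumptions. Set-up: 50 per arm, two strata of 25 per arm, a common odds ratio (OR), 20,000 simulated trials, two-sided 0.05. The LSM rate follows from p₁ = OR·o/(1 + OR·o), with o = p₀/(1 − p₀).

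- Unadjusted: X² = N(ad − bc)²/(r₁r₂c₁c₂).
- Cochran-Mantel-Haenszel (CMH): [Σ(a − r₁c₁/n)]² / Σ[r₁r₂c₁c₂/(n²(n − 1))], summed over strata.

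| Control rates by stratum | OR | LSM rates | Rejects, chi-square | Rejects, CMH |
|---|---|---|---|---|
| 10% / 10% | 1 | 10% / 10% | 0.050 | 0.049 |
| 5% / 35% | 1 | 5% / 35% | 0.036 | 0.051 |
| 5% / 60% | 1 | 5% / 60% | 0.016 | 0.051 |
| 5% / 35% | 4 | 17% / 68% | 0.72 | 0.80 |
| 10% / 40% | 3.5 | 28% / 70% | 0.73 | 0.79 |
| 3% / 50% | 4 | 11% / 80% | 0.51 | 0.73 |

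The first three rows are type I error, the last three power. The fall below 0.05 arises because the stratum is balanced between arms, as stratified blocks intend. Baseline ISI is not a stratification factor, so for it the expected cost is power rather than a conservative level; that case was not simulated.

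**Step 3: does baseline ISI predict response?** The article gives only pooled mean changes. If change is normal with the pilot mean and SD at every baseline, the chance of a drop of 8 or more (half-point cut) is:

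- LSM: 1 − Φ((7.5 − 6.82)/4.06) = 0.433
- Waitlist: 1 − Φ((7.5 − 3.24)/2.38) = 0.037

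These do not depend on b, because with entry at 8 or more the floor at 0 never blocks an 8-point drop. If change is instead proportional to baseline (assumed mean 15, SD 4.5, truncated at 8), LSM response is about 27% in mild and 56% in moderate or severe participants. The documents cannot separate the two models.

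The share of LSM participants reaching 0–7 who are classed as non-responders ran from 17% to 42% over assumed baseline means of 12 to 18 and both models.

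**The case against.** **Strongest case for the plan.** In a 1:1 randomised comparison the unadjusted test is valid. The 8-point cut is prespecified and referenced. Response and remission are different constructs, and choosing one is not an error. Mild participants' improvement is also captured by the full-scale ISI analyses and by the prespecified severity subgroups for the primary outcome. Power may be ample: with 0.433 against 0.037 and 50 per arm, unadjusted power is 0.999. All of this stands, and it limits the point to efficiency and clarity. The last figure, however, leans on a pilot of 12 per group.

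**Stronger readings that the documents do not support.**

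- A reader might infer that the rule cannot register remission in mild patients. It can: every mild entrant who drops 8 or more ends at 0–6, so every mild responder has left the insomnia range. The rule misses some such patients, not all.
- A reader might infer that response depends strongly on baseline. Step 3 shows that this follows from the proportional-change model and vanishes under constant change.
- A reader might infer that the response rate mixes treatment effect with case mix. Randomisation balances case mix in expectation, so the between-arm contrast is not biased by it.
- A reader might infer that imputation leaves no usable p-value. Chi-square statistics can be pooled across imputations, and so can risk differences or log odds ratios. Only Fisher's test lacks a standard route. Pooling details may also sit in an analysis plan that is not shown.

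**Remission is not simply better.** Under constant normal change, 0.940 of LSM and 0.875 of waitlist participants entering at 8 would reach 0–7, a difference of 0.065. Response differs by 0.433 − 0.037 = 0.396. At baseline 14 the remission difference is 0.531 − 0.085 = 0.446. Remission is therefore a companion, not a replacement.

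**Conclusion.** The concern holds in a limited form. The response rate is compared without the two covariates that section 2.9 uses for the continuous outcomes, one of which is the randomisation factor. This does not inflate type I error. If the stratum is prognostic the test is conservative (0.036 and 0.016 in two assumed cases), and power falls by 0.08, 0.06 and 0.22 in the three assumed alternatives. With no stratum effect the two tests hold the same level. These sizes depend wholly on assumed stratum rates. Section 2.8 does cite endocrine therapy as a risk factor for insomnia, which makes a stratum effect plausible but does not quantify it.

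That the 8-point rule is stricter than reaching ISI 0–7 at every mild baseline is certain from the protocol's own bands. How many participants this affects cannot be computed, because neither the baseline ISI distribution nor its relation to change is given.

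The imputation point is narrow: the rule fits Fisher's test poorly, and its literal scope reaches adverse events.

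The change is worth making because it is nearly free. The primary analysis and the sample size are untouched.

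**What to change.** 1. **Analysis of response.** Replace the unadjusted test by logistic regression on group, baseline ISI and endocrine status, and report the marginal risk difference with its confidence interval. State in advance a fallback to CMH by endocrine status if events are sparse. This is a real prospect: at 0.037, the waitlist arm would have 50 × 0.037 ≈ 2 responders. The fallback gives up adjustment for baseline ISI.
2. **Missing data.** Impute the ISI score, derive response within each completed data set, and pool the estimate by Rubin's rules.
3. **Scope of imputation.** Limit the sentence to efficacy data, so that adverse events are reported as observed.
4. **Optional.** Report the proportion with ISI of 7 or less at week 4 beside the 8-point response, or at least state that the two differ for mild entrants.

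Items 1 to 3 cost only wording, since all the variables are already collected. Item 4 adds one more secondary outcome.

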#### Mechanism outcomes

2.4.3

Blood and fecal samples will be collected from all participants at baseline and at the end of the treatment period (week 4). Fasting blood samples (20 mL) will be drawn from the antecubital vein between 7:00 and 9:00 AM. The samples will then be centrifuged at 3,000 rpm for 15 min at 4°C, and the resulting serum will be stored at −80°C. Fecal samples will be collected immediately after morning defecation, placed into sterilized fecal containers, and stored at −80°C. The mechanisms of LSM will be examined through serum biochemical markers, gut microbiota composition, and metabolomic profiling.

Serum biochemical markers will include neurotransmitters, inflammatory cytokines, and endocrine hormones. Neurotransmitters to be measured are 5-hydroxytryptamine (5-HT) and gamma-aminobutyric acid (GABA). Inflammatory markers will cover interleukin-1β (IL-1β), interleukin-6 (IL-6), and tumor necrosis factor-α (TNF-α). Hormonal analysis will focus on melatonin and hormones associated with the hypothalamic-pituitary-adrenal (HPA) axis, such as adrenocorticotropic hormone (ACTH), corticotropin-releasing hormone (CRH), and cortisol (CORT). All measurements will be conducted using enzyme-linked immunosorbent assays (ELISA).

Gut microbiota composition in fecal samples will be analyzed through 16S rRNA gene sequencing. α diversity will be assessed using observed ASV, Shannon, Simpson, and Chao1 indices, while β diversity will be evaluated through principal coordinates analysis (PCoA) based on the Bray–Curtis distance matrix. The linear discriminant analysis effect size (LEfSe) model will be applied to identify differentially abundant taxa between groups.

Metabolomic profiling of serum samples will be performed using non-targeted liquid chromatography-mass spectrometry (LC-MS) (26). Principal component analysis (PCA) and partial least squares discriminant analysis (PLS-DA) will be used to visualize metabolic patterns across groups. Key differential metabolites will be identified based on variable importance in projection (VIP) scores from the PLS-DA model. Additionally, non-targeted quantification of short-chain fatty acids (SCFAs) in fecal samples will be conducted via gas chromatography-mass spectrometry (GC-MS) (27).

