For the primary efficacy outcome (the change in the ISI score from baseline to the end of the 4-week treatment period), subgroup analyses will be conducted based on hypnotic medication use (yes, no) and insomnia severity (mild, moderate, severe) to further explore potential variations in the treatment effects of LSM across different subgroups. Additionally, sensitivity analyses will be performed for the primary efficacy outcome. Specifically, if missing values or non-normally distributed data are present, multiple imputation methods will be used to assess the impact of missing data, and generalized estimating equations will be employed as a non-parametric alternative for non-normally distributed data. Pre-specified per-protocol analyses will also be conducted. The per-protocol set will include all participants who completed the intervention and follow-up according to the study protocol. The results of the primary analysis will be compared with those from these sensitivity analyses to assess robustness.

All statistical analyses will be carried out using SPSS (version 26.0) and R (version 4.3.1). Two-tailed significance testing will be applied, with a *p*-value threshold of ≤ 0.05 indicating statistical significance.

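### Selecting untargeted metabolites by PLS-DA VIP score has no error control, so at least one false metabolite–ISI link is near certain; the nine-marker serum panel is much less exposed

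*Protocol article*

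**What the plan says.** Section 2.4.3 (Mechanism outcomes) of the protocol article sets out three layers of mechanism data, sampled at baseline and week 4.

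- **Serum markers.** "Serum biochemical markers will include neurotransmitters, inflammatory cytokines, and endocrine hormones". Nine are named: 5-HT, GABA, IL-1β, IL-6, TNF-α, melatonin, ACTH, CRH and cortisol.
- **Microbiota.** "α diversity will be assessed using observed ASV, Shannon, Simpson, and Chao1 indices". For taxa, "The linear discriminant analysis effect size (LEfSe) model will be applied to identify differentially abundant taxa between groups".
- **Metabolites.** The platform is untargeted: "Metabolomic profiling of serum samples will be performed using non-targeted liquid chromatography-mass spectrometry (LC-MS". The selection rule is "Key differential metabolites will be identified based on variable importance in projection (VIP) scores from the PLS-DA model". No cut-off or check against chance accompanies it.

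Section 2.9 (Statistical analysis) gives t-tests or Mann–Whitney U tests for serum markers and taxa abundance. It then states: "Correlation analyses between ISI scores, differential serum biochemical markers, differential metabolites, and key gut microbiota will be performed using Pearson or Spearman correlation coefficients". For all analyses, "Two-tailed significance testing will be applied", with a threshold of p ≤ 0.05. No multiplicity adjustment is mentioned. The article does not say whether the correlations pool the arms.

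**The concern.** VIP ranks features by their share of a fitted PLS-DA model and tests nothing. PLS-DA with more features than participants separates the arms in noise, and VIP then ranks that noise. The stated rule therefore cannot in practice return the answer that no metabolite differs.

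The second step compounds this. Features chosen because they differ by arm are correlated with ISI, and the pilot in section 2.8 leads one to expect ISI to differ by arm too. If the arms are pooled, the shared arm difference alone creates correlation.

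At stake is the mechanistic half of the report. The Introduction presents efficacy and mechanism as joint objects of evaluation, and the Discussion expects the multi-omics results to lend substantial support to the treatment's effects. A list of metabolites linked to ISI would appear whether or not such links exist.

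**Working it through.** **1. Inputs and the plan's own figure.** The article states no error rate or feature count for the mechanism analyses. The only figures to reproduce are in section 2.8.
- Pilot ISI decrease: 6.82 (SD 4.06) against 3.24 (SD 2.38). d = 3.58 / √((4.06² + 2.38²)/2) = 3.58 / 3.328 = 1.08, as stated.
- A Welch t-test at two-sided 0.05 and 90% power needs 20 per group (power 0.909; 19 gives 0.893). With 10% dropout, 20/0.9 rounds up to 23. Two strata give 46, as stated before rounding to 50.
- Used below: 50 × 0.9 = 45 per arm, with ISI change drawn from the pilot means and SDs.
- Assumed: cut-off VIP > 1, two PLS components, 100 to 3,000 features.

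**2. Why VIP always selects.** VIP_j² = p · Σ_a(S_a · w_ja²) / Σ_a S_a, where S_a is the variation in arm explained by component a and the squared weights sum to 1 over features. Summing over j gives p, so the mean of VIP² is exactly 1 and the largest VIP can never fall below 1. With many independent noise features, VIP² behaves roughly like a χ² variable on 1 df, and P(χ²₁ > 1) = 0.317. About 32% should therefore pass by chance.

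**3. Simulation with no feature related to arm or ISI** (200 trials per setting; independent features / features in blocks with within-block r = 0.5):

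| Features | Share with VIP > 1 | Pooled ISI correlation p ≤ 0.05 among these | At least one selected and correlated, arms pooled | Same, within arm |
|---|---|---|---|---|
| 100 | 35% / 40% | 7.7% / 6.6% | 94% / 87% | 86.5% / 74% |
| 200 | 34% / 38% | 8.7% / 8.0% | 99.5% / 97% | 97% / 90.5% |
| 500 | 33% / 37% | 8.7% / 7.9% | 100% / 100% | 100% / 100% |
| 1,000 | 32% / 35% | 8.7% / 7.8% | 100% / 100% | 100% / 100% |
| 3,000 | 32% / 33% | 8.9% / 8.5% | 100% / 100% | 100% / 100% |

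Hand check for 100 independent features: 1 − (1 − 0.077)^35 = 0.94. At 500 features the mean number of false metabolite–ISI links is about 14 pooled and 8 to 9 within arm. Most of the problem thus comes from selection and multiplicity, and pooling adds to it.

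**4. Pooling for p-selected features.** Among null features selected at p ≤ 0.05, the pooled correlation with ISI was significant for 16.0% to 18.8%, or about 15–19% allowing for simulation error. Within arm it was about 5%. The inflation depends on the ISI effect: at d = 0.5 the p-selected rate falls to about 8%, and at d = 0.3 to about 6%.

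**5. Serum panel.** For nine independent tests, 1 − 0.95⁹ = 37%, with 9 × 0.05 = 0.45 false differences expected. With an assumed common correlation of 0.3, 0.5 or 0.7 between markers, this falls to 33%, 27% or 20%. The full chain (a marker falsely selected and then correlated with ISI in pooled arms) occurs in about 7% of trials.

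**The case against.** The strongest reply is that a journal article condenses a fuller plan. A VIP cut-off, permutation check, LEfSe thresholds, FDR families and correlation covariates could all sit there, and a 0.05 threshold is compatible with adjusted p-values. This stands for everything on which the article is merely silent. It does not rescue the metabolite rule, because VIP is stated as the basis of selection and no choice of threshold turns a relative ranking into an error-controlled test.

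Three stronger readings are tempting and are not supported.
- **That false findings are near certain across all mechanism data.** This holds for the untargeted metabolites only. The serum risk is 37% at most for independent tests, and the Discussion itself describes several of these markers as biologically linked. Taxa are selected by LEfSe with no thresholds given, so no error rate can be put on that step.
- **That the correlations ignore arm.** Section 2.9 states neither pooling nor stratification. The inflation in step 4 is conditional on pooling.
- **That pooling is the main fault.** The 15–19% rate belongs to p-selected features at the pilot effect, which comes from only 12 per group. For metabolites selected by VIP it is about 7–9% against a nominal 5%.

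It is also fair to say that the Abstract speaks of exploring mechanisms, that these outcomes are listed apart from efficacy, and that the sample size rests on ISI alone. That limits the importance of the point. But no section tells the reader to treat the mechanism results as hypothesis-generating.

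**Conclusion.** The concern holds for the untargeted metabolomics. Followed as written, the rule yields differential metabolites in pure noise (about 32–40% of null features above VIP 1). It makes at least one false metabolite–ISI link near certain: about 87–94% at 100 features and about 100% at 500 or more. These figures rest on 45 per arm, an assumed cut-off of 1 and an assumed feature count; the conclusion is the same across the range examined.

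It holds in milder form for the nine serum markers: at most 37% for any false difference if independent, less if correlated. If the correlations pool the arms, the false-correlation rate is about 7–9% for VIP-selected and 15–19% for p-selected null features at the pilot ISI effect, and lower if the true effect is smaller. The primary ISI comparison does not use these data and is unaffected. The change should be made before the mechanism data are analysed.

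**What to change.** 1. Call a metabolite differential only if it passes Benjamini-Hochberg control (q < 0.05) in a between-group test. Keep VIP as a secondary ranking, shown only if the PLS-DA model passes a label-permutation check.
2. Apply false discovery rate control within the serum markers, within taxa and within the set of correlations.
3. Compute marker–ISI correlations within arm or adjusted for arm, and say which.
4. Label the mechanism results exploratory, and temper the Discussion accordingly.

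Under the same null simulation, step 1 cuts the chance of any falsely selected feature to 2.5–6.5%. Unpooling the arms returns the false-correlation rate to about 5%. Step 3 alone is not enough, since 8 to 9 false links per trial remain at 500 features.

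The cost is analysis code only; no further samples or visits are needed. Fewer features will be declared, with some loss of sensitivity.
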